## Abstract

**Background:**

The physiological and psychological signalling between mother and infant during lactation is one of the prominent mother-infant factors that may influence breastfeeding outcomes. The infant can ‘signal’ his needs through vocalisation, and the mother can respond by allowing or restricting nipple access, which might alter the breast milk composition or volume. This may lead to parent-offspring conflict during the lactation period. Challenging infant behaviour has also been associated with maternal psychological distress, which might affect breastfeeding performance. Most attempts to improve breastfeeding rates focus on providing additional support, yet many aspects of the breastfeeding process are poorly understood. Thus, our objective is to investigate mother-infant signalling during breastfeeding by manipulating maternal psychological state using a relaxation therapy intervention. The study will test the hypothesis that mothers who listen to the therapy will be more relaxed/less stressed and this will favourably alter breast milk composition and/or affect milk volume and hence influence infant outcomes.

**Methods:**

A randomised controlled trial will be conducted in first-time breastfeeding mothers and their new-born infants. Pregnant mothers will be recruited at antenatal clinics in Selangor, Malaysia, and four home visits will be carried out at 2, 6, 12 and 14 weeks postnatally. Participants will be randomised into a control and an intervention group in the early post-partum period. Mothers from the intervention group will be asked to listen daily to an audio recording with relaxation therapy during breastfeeding. Maternal psychological state, breastfeeding practices and infant behaviour will be assessed using validated questionnaires. Milk volume will be measured using stable isotopes. Breast milk samples will be collected to measure macronutrient content and hormone levels. Anthropometric measurements (weight, length and head circumference) will be performed during all home visits, including body composition at week 14.

**Discussion:**

The main outcomes will be the effect of the intervention on maternal psychological state, milk production, cortisol levels, and infant behaviour and growth. Secondary outcomes will be associations between breast milk composition and infant appetite and growth. This study aims to provide a greater understanding of maternal-infant factors which influence breastfeeding outcomes and which may be useful targets for future interventions.

**Trial registration:**

ClinicalTrials.gov identifier: NCT01971216.

## Background

Mother-infant signalling involves communication and interaction between a mother and her infant. The factors involved in mother-infant signalling in early infancy can be broadly categorised as psychosocial or physiological. The psychosocial aspects such as physical contact, maternal psychological state and infant behaviour occur in all mother-infant pairs, regardless of their feeding method. However, physiological mechanisms are unique to breastfed infants and their mothers because during breastfeeding, milk synthesis and milk composition do not solely reflect maternal physiological and psychological processes. Breastfeeding also represents a complex physiological and behavioural negotiation between the mother and the offspring [1, 2]. For example, the infant can ‘signal’ his needs through vocalisation or non-nutritive suckling, and the mother can respond by allowing/restricting nipple access, hence down- or up-regulating milk synthesis and affecting milk volume. She can also alter the breast milk composition resulting in different concentrations of macronutrients or bioactive factors. This may result in a competition for energy between a mother and her infant during the lactation period, which is described as parent-offspring conflict. Thus, breastfeeding should not be regarded as a one-way communication or an inevitably harmonious cooperation between the mother and the infant, but rather as a dynamic process which involves complex psychosocial and physiological signalling between both parties [1].

This relationship between infant behaviour and maternal response in terms of breastfeeding behaviour or the composition of milk, particularly bioactive factors (e.g. hormones) in breast milk, is largely unexplored in humans. Moreover, all of these factors are complex and inter-related. Therefore, there is a need for research to explore the non-nutrient components in breast milk that may act as messengers in breastfed infants, potentially affecting the infant’s behaviour and metabolic regulation. For example, infant behaviour and temperament in early life may be affected by the concentrations of certain hormones or endogenous opiates such as cortisol and endorphins [3, 4]. Naturally occurring opiate substances in breast milk such as ß-casomorphins [5] may act as sedatives, and hence blunt or lower infant appetite, whereas ghrelin and leptin may influence feeding behaviour (affecting appetite and satiety) and are suggested to be major factors involved in metabolic regulation in breastfed infants [6]. Therefore, studies have hypothesised that mothers have the potential to shape infant behaviour in early life by the transmission of biologically active compounds including cortisol in milk during breastfeeding [3, 7, 8]. Other studies also suggest that breast milk hormones may influence infant appetite and feeding pattern, which can influence growth and body composition in early and later life [9, 10]. Therefore, to address this, as part of this trial, we will investigate breast milk hormones (cortisol, ghrelin and leptin concentrations) in relation to infant behaviour and growth in early infancy.

Although there are many interesting and unexplored issues in the signalling between mother and infant during breastfeeding, the complexity of the inter-relationships between factors makes it problematic to define cause and effect using an observational study design. Thus, many aspects of the breastfeeding process remain poorly understood, and most attempts to improve breastfeeding rates mainly focus on providing additional support, for example improving maternity leave or providing BF support via groups and organisations, rather than on understanding maternal and infant factors in early life. Therefore, to explore these factors in early human life, we plan to use an experimental approach to investigate causal relationships between maternal psychological state, manipulated using a randomised relaxation intervention, and breast milk volume and composition and infant behaviour and growth. We hypothesise that maternal psychological state is associated with breast milk production which will have consequent effects on infant feeding behaviour and growth. This is because emotional distress in mothers has been reported to inhibit the let-down reflex leading to disruption of milk flow and reduced milk volume [11, 12]. Conversely, milk ejection can be improved by relaxation therapy, as demonstrated in previous studies using relaxation techniques such as guided-imagery and music therapy. Randomised studies in mothers of premature infants found that mothers who listened to guided relaxation/imagery recordings (as a relaxation therapy) produced significantly more milk than control groups [13, 14], but to our knowledge this type of intervention has not been formally tested in mothers who are breastfeeding their healthy term infant, and none of the previous studies investigate the consequent effects on infant outcomes.

In summary, this study aims to investigate the signalling between mother and infant in early life, using an experimental approach to determine causal relationships between maternal psychological state and milk intake, milk cortisol levels, and the consequences for infant behaviour and growth. Other mother-infant factors such as changes in milk leptin, ghrelin and macronutrient concentrations within a feed, infant appetite and temperament will be studied as secondary outcome measures. The results may identify modifiable factors which can be used to encourage and support breastfeeding, including increasing breastfeeding rates. The study, named the Mother-Offspring Milk (MOM) Study, is intended to fill current research gaps by investigating both psychological and physiological mother-infant factors during breastfeeding and by using a more robust methodological design. This manuscript describes the rationale and design of the MOM Study.

## Methods/Design

### Study design

This is a randomised controlled trial that involves first-time healthy breastfeeding (BF) mothers and their full-term infants (*n* = 64 mother-infant dyads). The objective is to identify causal effects of maternal psychological state, manipulated using a relaxation intervention on breast milk volume and composition and infant outcomes (behaviour and growth). In general, this study investigates the mother-infant signalling during breastfeeding and aims to provide a greater understanding of maternal-infant factors which influence the breastfeeding outcomes such as milk yield or milk energy, and which may be useful targets for future interventions.

### Hypotheses and outcome measures

Primary hypotheses: The use of a relaxation tape by breastfeeding mothers starting at week 2 postpartum will result in:i.reduced maternal stress and anxietyii.the production of a higher volume of breast milkiii.lower milk cortisol concentrationsiv.favourable effects on infant behaviour (less crying, more sleeping)v.differences in infant body composition

Measures (i) - (v) will be assessed at baseline (week 2) and at 12 weeks in both control and intervention groups to ascertain the long-term effects of the relaxation therapy. Measures of (iii) will also be assessed pre and post a single breast-feed in both groups at 2, 6 and 12 weeks to ascertain the short-term effects of the relaxation therapy. The primary comparison will be the values at 12 weeks adjusted for the baseline value, compared between the two groups. Measures of body composition (v) will also be assessed at 14–16 weeks postnatally.

The primary outcomes will be assessed as follows:i)maternal stress and anxiety assessed using the Cohen’s Perceived Stress Scale (PSS) and Beck Anxiety Inventory (BAI) respectively (at 12 weeks)ii)breast milk volume at 12 weeks assessed non-invasively using stable isotope techniquesiii)breast milk cortisol concentrations at 12 weeksiv)infant behaviour measured using a 3-day diary at 6 weeksv)infant weight and body composition measured using stable isotopes at 12 weekschanges in maternal saliva cortisol, breast milk cortisol and milk volume before and after a breastfeeding session at 2, 6 and 12 weeks.

b) Secondary hypotheses:i.Infant temperament, behaviour and gender influence milk intake and hence early growth and body composition.ii.Milk composition including non-nutrient factors in breast milk (hormonal constituents; ghrelin and leptin) influence infant appetite and feeding patterns and hence infant growth and body composition

The secondary outcome measures will be:i.non-nutrient factors in breast milk – leptin and ghrelinii.macronutrient composition and milk energy (fat, carbohydrate, protein and total calorie)iii.infant temperament measured using the Revised-Infant Behaviour Questionnaire (R-IBQ)iv.infant appetite assessed using the Baby Eating Behaviour Questionnaire (BEBQ)v.maternal depression assessed using Edinburgh Postnatal Depression Scale (EPDS

### Sample size and study population

The target sample population will be first-time mothers and their newborn infants living in Klang-Valley, Malaysia. The conventional formula [15] for two sample t-test is used to determine the number of infants required to detect a difference between two groups; control and intervention:$$ \mathrm{n}=16\ \left({\mathrm{SD}}^2/{\mathrm{D}}^2\right) $$where *n* = number per group, *SD* = standard deviation, *D* = difference between groups.

Hence, a sample of 56 infants (28 per randomised group) would allow the detection of a 0.76 SD difference in milk volume between groups at 80% power with a significance level of α = 0.05 (D = 0.76, SD = 1); this is a biologically plausible difference based on previous studies of the effect of relaxation interventions on milk volume production between control and intervention groups of mothers with preterm infants [13]. Since this study will involve mothers with healthy full-term infants, the effect size may be smaller than the previous study, as mothers with preterm infants are likely to be more stressed. Therefore, to allow for a smaller effect size as well as for drop-outs or failed measurements, it is planned that 80–100 pregnant women will be recruited.

### Recruitment

Recruitment will be performed at selected antenatal clinics in Selangor, where pregnant mothers in the second or third trimester of pregnancy will be approached. Mothers who are planning to exclusively breastfeed and interested in participating in the study will be given an information sheet, and the practical details will be explained. If they are still interested, screening questions will be asked to determine if they meet the eligibility criteria (see below). If participants meet the eligibility criteria, written informed consent will be obtained and they will be enrolled into the study. Contact details will be obtained from them, including their estimated day of delivery (EDD). Mothers will be contacted by the researcher 3 to 7 days after their EDD to check if they have delivered their baby, are breastfeeding and still willing to participate in the study. All participants were also provided with the MOM Study’s contact information if they would like to inform about their birth. At this stage, all participants will be screened again to assess the eligibility criteria for both the mother and baby. If they are eligible and still interested in participating in the study, a home visit will be arranged. Mothers will also be advised that if for any reason and at any time they do not wish to be contacted, they can inform the researcher. All participants will also be offered a manual breast pump (Philips Avent brand) as a token of appreciation.

Advertisements about the study will also be posted on parenting and nutrition websites including organizations’ website such as the Malaysia Breastfeeding Peer Counsellor Group, Nutrition Society of Malaysia and Malaysia Dietetic Association. Flyers and posters will be displayed in places commonly visited by mothers such as private antenatal clinics or hospitals, nursing rooms or baby care rooms at shopping malls or restaurants, health care centres and childcare shops in Selangor, Malaysia. Table 1 shows the eligibility criteria for mothers and infants.

**Table 1 Tab1:** Eligibility criteria for mother and infant

First screening	Inclusion criteria	Exclusion criteria
Mother (during pregnancy)	Primiparous mother with singleton pregnancy	Multiparous mother or mother of twin pregnancy
	Free from serious illness/chronic disease.	Taking medication for illness or chronic disease.
	Non-smoker	Smoker
	Understands Malay or English	Does not understand Malay or English
Second screening		
Mother (after birth) Infant	Free of illness that can affect breastfeeding	Mother has illness that prevented her from breastfeeding
	Exclusively breastfeeding at 2 weeks	Mixed- or not breastfeeding at 2 weeks
	Interested in participating further	Not interested or unwilling to arrange home visit
	Full-term infant (37–42 weeks of gestation)	Preterm infant (<37 weeks of gestation)
	Infant birth weight of ≥2500 g	Infant birth weight of <2500 g
	Free from serious illness that could affect nursing or growth	Has illness that could affect nursing or growth

### Data collection

In this section, the process of data collection is explained first, including the tools used for measurement and assessment. Next, a detailed description of each tool and measurement is provided, including information about the development of the intervention tool. Research flow charts illustrating the overview plan of the study and the overall data and sample collection procedures are shown in Figs. 1, 2 and 3.

**Fig. 1 Fig1:**
[figure not shown]
Overview of the MOM Study plan

**Fig. 2 Fig2:**
[figure not shown]
Recruitment, enrolment and randomisation process

**Fig. 3 Fig3:**
[figure not shown]
Data collection processes and procedures

#### Post-enrolment session

Once signed consent has been obtained, participants will be provided with questionnaires to be completed immediately following enrolment at the antenatal clinic, namely the socio--demographic questionnaire and Iowa Infant Feeding Attitude Scale (IIFAS) questionnaire.

#### Randomisation

Prior to the first home visit (at 2–3 weeks after delivery), and after confirming that the mother is still eligible and wishes to continue in the study, the mother will be randomised to either the control group or the relaxation group. Randomisation will be stratified by ethnicity: Malay or Bumiputera, Chinese and Indian. Mothers will not be informed about this process as doing so will most likely influence their behaviour. Thus, the mothers will be blinded to the randomisation process in order to prevent the mothers in the control group from seeking or using some form of relaxation therapy, if the possibility of it being beneficial has been raised. However, they will be informed that the MOM Study is investigating the effects of maternal mood as well as infant factors on breastfeeding at a general level. The randomisation schedule will be generated by computer in randomised blocks of permuted length (2,4,6). Assignments will be prepared by a member of the research team in London who does not have contact with the subjects and assignments will be held in sealed opaque envelopes. Each assignment will be revealed by the researcher on the day, just before the first home visit, in order to prepare the intervention materials including the diary log specifically for mothers in the intervention group. There will be a low possibility of contamination between randomised groups since home visit sessions will be performed over a large geographical area in the central region of Malaysia. Therefore, the mothers in the intervention group will not be likely to have the opportunity to reveal the existence of the intervention tool to mothers in the control group. All mothers will only be informed about the randomisation process when the trial has been completed, when they receive a summary of the results.

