### Plan of statistical analysis

Data that are later found to be ambiguous will be flagged up and re-checked, and mothers will be contacted for clarification where necessary. Data will be recorded initially in Excel datasheets and later exported to SPSS. All questionnaires and anthropometric data will be analysed using IBM SPSS (version 23). Normality of continuous data will be assessed by Q-Q Plot, histogram and will also be tested by the Kolmogorov-Smirnov Test. The main analysis will be an intention-to-treat analysis comparing the difference between groups in the final outcome adjusted for the baseline value where data are available using independent t-tests. Independent t-test and repeated measures will be used to examine changes in milk intake and other milk components including cortisol levels between groups and between time points respectively as secondary analyses. For the secondary outcomes, associations between infant temperament/behaviour and milk volume, milk composition, infant growth and body composition will be examined using univariate analyses. Correlation and regression analysis/MANOVA will then be used to adjust for confounding factors. Interaction terms will be introduced where appropriate, especially in the multivariate analysis. The cut-off used for significance will be set at *p* < 0.05. Although multiple testing will be done to test the outcomes, the *p*-value cut-off point will not be adjusted for multiplicity since the different outcome measures are independent of each other.

Anthropometric data will be converted to standard deviation score (SDS, Z-score) for infant weight, height, head circumference and BMI using WHO 2006 standard data (LMS growth add- in for Microsoft Excel) and SDS will be used in all analyses. The weight data at the final time point will be compared between groups and adjusted for baseline weight as the primary outcome measure for growth using the LMS ‘Weight gain to SDS’ based on the WHO 2006 growth standard data (ie. external data). This method takes into account the baseline weight (HV1) in calculating the change from baseline to an endpoint or increase in weight between two-points of measurements. An increment of more than 1 band on the WHO growth chart or ±0.67 SD between measurements will be considered as representing ‘rapid weight gain’ [35].

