## Discussion

The majority of the population in Malaysia, especially first-time mothers, practice a traditional postpartum confinement period for about 30–45 days, according to the cultural tradition of their ethnic background [36]. During this period, the mother and her infant will be taken care of either by their family members, particularly the infant’s grandmother, or by a confinement lady who will be paid to stay overnight with the mother or come to the house on a daily basis. The caretaker will usually prepare meals for breakfast, lunch and dinner following the cultural confinement diet for the mothers, and will also perform special postpartum traditional massage on the mother, especially during the first 3 weeks of the postnatal period [36]. The caretaker will also help to take care of the infant by changing the nappy, bathing or holding the infant when necessary. This is because the mother is encouraged to minimise physical activity and have ample rest to recover from the birth [36]. This confinement practice should facilitate the trial since all mothers in the study will receive similar care.

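### Randomisation is stratified by ethnicity, but the stated main analysis adjusts only for the baseline value; adding the stratum is a small, free gain in precision

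*Protocol article*

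**What the plan says.** **Design.** The Randomisation section of the Protocol article states: "Randomisation will be stratified by ethnicity: Malay or Bumiputera, Chinese and Indian". The schedule uses permuted blocks of 2, 4 and 6.

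**Main analysis.** Hypotheses and outcome measures states: "The primary comparison will be the values at 12 weeks adjusted for the baseline value, compared between the two groups". The Plan of statistical analysis describes a main analysis by intention to treat: "comparing the difference between groups in the final outcome adjusted for the baseline value where data are available using independent t-tests". Neither place mentions ethnicity.

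**Other adjustment.** The same section adds: "Correlation and regression analysis/MANOVA will then be used to adjust for confounding factors". This follows the sentence on associations among the secondary outcomes and names no covariate.

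**Ethnicity and care.** The Discussion says that mothers follow a postpartum confinement period of about 30–45 days "according to the cultural tradition of their ethnic background". It then concludes that mothers in the study will be cared for in much the same way.

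**Size.** Sample size and study population states that "a sample of 56 infants (28 per randomised group) would allow the detection of a 0.76 SD difference in milk volume between groups". The calculation takes α = 0.05 and a power of 80%. Study design gives 64 dyads, and 80–100 women are to be recruited in pregnancy.

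**The concern.** Stratified blocks force the arms to be nearly balanced within each ethnic group. Differences between ethnic groups therefore contribute little to the actual variability of the arm difference. An analysis without the stratum still counts those differences as residual noise. Its standard error is then larger than the design warrants, its confidence intervals are a little wide, and its type I error falls below the nominal 5%.

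What is at stake is precision. The protocol concedes that the effect in mothers of term infants may be smaller than the one the trial was sized for, so precision that costs nothing is worth having.

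**Working it through.** **1. The plan's own figure.** With D = 0.76 and SD = 1, n = 16/0.76² = 27.7, rounded up to 28 per group. This reproduces. Exact power of the two-sided t-test is 79.8% at 28 per group and 84.9% at 32 per group (64 dyads).

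**2. Assumed inputs.** The documents do not give R², the share of outcome variance explained by ethnicity, or the ethnic mix. R² is taken as 0.02, 0.05 and 0.10.

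**3. No baseline value.** The sections on home visits 3 & 4 and on infant body composition place the infant isotope measurement at the fourth visit only, so there is no baseline to adjust for. The ratio of the standard error without the stratum to that with it is approximately 1/√(1 − R²).

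**4. Baseline value adjusted for.** Assume total variance 1 at both times, the same ethnic shift at both times, and within-stratum correlation ρ between baseline and follow-up. The overall correlation is r = R² + (1 − R²)ρ.

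- Residual variance given baseline only: 1 − r²
- Residual variance given baseline and stratum: (1 − R²)(1 − ρ²)
- Ratio of standard errors: √[(1 − r²)/((1 − R²)(1 − ρ²))] = √[1 + R²(1 − ρ)/(1 + ρ)]

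For ρ = 0.3, (1 − ρ)/(1 + ρ) = 0.7/1.3 = 0.538. For ρ = 0.7 it is 0.3/1.7 = 0.176.

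| R² | No baseline | Baseline, ρ = 0.3 | Baseline, ρ = 0.7 |
|---|---|---|---|
| 0.02 | 1.010 | 1.005 | 1.002 |
| 0.05 | 1.026 | 1.013 | 1.004 |
| 0.10 | 1.054 | 1.027 | 1.009 |

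The equal-shift assumption matters. An ethnic difference that arose only after baseline would not be absorbed by the baseline value, and the ratio would then be at least that in the no-baseline column.

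**5. Simulation of the design without a baseline value.** Settings: 56 dyads, three strata in an assumed 70/20/10 mix with equally spaced means, blocks of 2, 4 and 6, and 8,000 trials per scenario. The Monte Carlo standard error at 5% is √(0.05 × 0.95/8000) = 0.24 points.

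| R² | Type I error, without / with stratum | Power at 0.76 SD, without / with stratum |
|---|---|---|
| 0 | 5.0% / 5.1% | 80.5% / 80.0% |
| 0.05 | 4.4% / 4.8% | 80.4% / 81.5% |
| 0.10 | 4.4% / 5.4% | 81.1% / 83.6% |
| 0.20 | 3.3% / 5.1% | 81.6% / 87.3% |

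At R² = 0.10 the mean standard error is 0.266 without the stratum and 0.253 with it, a ratio of 1.05. The actual standard deviation of the unadjusted estimate is 0.258, so that analysis overstates its own error by 0.266/0.258 = 1.03, or about 3%. The two ratios differ mainly because incomplete blocks leave a little imbalance within strata. Mixes of 90/5/5 and 50/35/15 give similar results at R² = 0.10: type I error 4.2% and 4.1%, with 2.6 and 2.8 points of power lost.

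**The case against.** The strongest reply is that the point is small and perhaps already handled.

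- **An article condenses a fuller plan, and covariates are often left to the analysis plan.** This has weight, but the article is not silent. In two places it defines the main comparison with one adjustment, and in one of them it names the test. The sentence on regression and MANOVA does not rescue it, because it concerns secondary associations and names no covariate.
- **The article does not show that ethnicity is prognostic.** This stands. A reader might infer it from the Discussion, where confinement follows ethnic tradition. The same paragraph draws the opposite conclusion, that care will be similar. Confinement also ends before the 12-week comparison, and nothing in the article links ethnicity to milk volume, stress, cortisol or growth.
- **The baseline adjustment already absorbs stable ethnic differences.** This stands for outcomes with a baseline value, under the equal-shift assumption, and it cuts the excess to about half or less. It does not help outcomes measured once.
- **Power is not as tight as 56 dyads suggests.** This stands in part: 64 dyads give about 85% power for 0.76 SD. The protocol itself allows that the true effect may be smaller.

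**Conclusion.** The mismatch between design and stated analysis is real, and its consequence is modest. For R² between 0.02 and 0.10, the excess in the standard error is roughly 0 to 3% with a baseline value and an equal ethnic shift at both times. Without a baseline value the ratio of standard errors reaches about 1.05. The excess is nil where ethnicity does not predict the outcome, so the loss cannot be claimed for every comparison.

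Three stronger readings are tempting, and the documents do not support them:

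- **The results would be biased or the false-positive rate inflated.** The error runs the other way: the test is slightly conservative.
- **The sample size is wrong.** It reproduces, and it assumes no gain from stratification.
- **About 6 of 56 dyads are wasted.** That comes from R² = 0.10 with no baseline adjustment (25 rather than 28 per arm). With baseline adjustment the squared ratios of 1.018 to 1.054 correspond to 56 × (1 − 1/1.018) ≈ 1 to 56 × (1 − 1/1.054) ≈ 3 dyads.

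This is a free improvement and no threat to the trial's validity.

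**What to change.** In the Plan of statistical analysis, replace the independent t-test for between-arm comparisons with a linear model (ANCOVA). It should contain arm, the baseline value where available, and the ethnicity stratum as a fixed factor with three levels. A factor cannot be added to a t-test, so the test itself has to change. The same change resolves a looseness in the current wording, since an independent t-test on final values cannot adjust for baseline.

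Add a rule for very small strata, set before the outcome data are analysed. For example, a stratum with fewer than two dyads in either arm is merged with the next smallest.

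The cost is a short change of text and two degrees of freedom. Ethnicity has to be known for randomisation and is recorded in the socio-demographic questionnaire, so no new data are needed. If ethnicity turns out not to matter, the simulated price is negligible: 80.0% power with the stratum against 80.5% without it.
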